### Primary outcome measures

The primary outcomes are i) participants’ ratings on perceived knowledge regarding adolescent suicidality, ii) perceived self-confidence when interacting with suicidal adolescents, and iii) actual knowledge regarding adolescent suicidality.

Since this is the first time e-learning modules on adolescent suicide prevention for gatekeepers have been developed and in order to test their effectiveness, the authors have composed three questionnaires to test the three primary outcomes of this study. This was done in collaboration with adolescent suicide prevention experts involved in this project. In order to test the first and the second primary outcome measures, two short questionnaires have been developed consisting of statements to be endorsed on a three-point Likert scale (0 = disagree, 1 = partially agree, 2 = agree).

The questionnaire measuring perceived knowledge consists of nine items. The first item is a general statement about the overall knowledge of the participants when it comes to adolescent suicide prevention (‘I have sufficient knowledge about the process of recognition, guidance, and referral of suicidal youth’), and the remaining eight statements each capture the essence of one of the eight modules offered. For example, the fifth module focuses on how to engage in a conversation with a suicidal adolescent and the statement measuring the perceived knowledge regarding this module is ‘I have sufficient knowledge to engage in a conversation with a suicidal adolescent’. The questionnaire measuring perceived self-confidence consists of 16 items, each capturing the required skills and attitudes in adolescent suicide prevention which are addressed in the eight modules. Examples of the statements are ‘I can adequately provide first aid to a young person who has attempted suicide’ and ‘I can make a distinction between my duties and those of a therapist’. During the three assessments of the effectiveness study participants receive the same two questionnaires.

To assess the last primary outcome, actual knowledge, six cases have been developed. Each case starts with a photo of and some characteristics about an imaginary adolescent (name, age, and education are added), and is followed by three informational segments. The segments provide information about the background, friends, and family circumstances of the adolescent. After reading each case, the participant is asked to answer several questions on potential suicidality of which two are general questions (yes/no) and eight questions with multiple choice answers of which one is correct, covering the content of each of the eight e-learning modules. The number of questions the participant has to answer depends on the answers given on the general questions. During each assessment (T₀, T₁, T₂) participants will be presented with two new cases.

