### Statistical analysis plan

The internal consistency reliability of the three questionnaires will be estimated with Cronbach’s alpha and exploratory factor analysis will be used to check for dimensionality.

To test whether the knowledge of gatekeepers and the gatekeeper’s self-confidence increases after gaining access to the website, mean differences of the two groups (experimental and waitlist control) on the three questionnaires will be compared for the three assessment points.

Both analysis of covariance (ANCOVA) and hierarchical linear modeling (HLM) are suitable methods to test the hypotheses of this randomized pre-test, post-test, and follow-up design
[19].

An ANCOVA in which pre-test is used as a covariate can be used to test for group differences from pre-test to post-test, from pre-test to follow-up, and from post-test to follow-up. By including the pre-test as a covariate in the model, more statistical power and statistically accurate confidence intervals of the differences of means between the experimental group and the waitlist control group will be gained
[19]. Missing data will be dealt with by multiple imputation
[20-22]. Alternatively, HLM may be used in which individual growth curves over time are integrated in the model
[19,23]. HLM assumes that data are missing at random
[24].

The data from the evaluation questionnaire, which is only completed by participants from the experimental group, will be analyzed using descriptive statistics. All analyses will be carried out on intention-to-treat sample.

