## Discussion

This randomized controlled trial will test the effectiveness of e-learning modules on adolescent suicide prevention in promoting knowledge and self-confidence in gatekeepers dealing with this subject.

The use of e-learning modules for adolescent suicide prevention is expected to be beneficial for gatekeepers for several reasons. First, the subject of suicide is surrounded with stigma and taboo which can hamper gatekeepers to actively seek information on this topic through participation in face-to-face training courses. By offering the training online, gatekeepers will have access to information on the required steps in adolescent suicide prevention from their own home or workplace. Second, gatekeepers, especially those working in schools, do not always have the required resources and time to participate in face-to-face training sessions. The online character of the program’s modules gives gatekeepers the opportunity to have access to the program 24/7 from any given location. By offering the program in divided short modules, gatekeepers have the opportunity to compose their own personal training based on their own pre-existing knowledge, experience, and needs. This way, they are no longer obliged to attend an extensive training while they may only be interested in a small segment of the training offered. Third, these e-learning modules can be developed and maintained with limited resources, which allows the training to be offered for free. Since the modules are offered online, gatekeepers from all over the nation can have access to the program immediately.

The main limitation of this study has to do with the questionnaires used during the three assessments. Since this is the first time e-learning modules on adolescent suicide prevention have been developed for gatekeepers and are being tested in a randomized controlled trial, three questionnaires had to be developed in order to measure the three outcome measurements of this study. Thus, the questionnaires have not yet been validated and the current trial is the first to provide information on the usefulness of the questionnaires. If this line of research will gain popularity and more randomized controlled trials will be carried out in this area, it is recommended that validated questionnaires should be developed and used to test the effectiveness of e-learning modules on adolescent suicide prevention by gatekeepers.

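### Actual knowledge is tested with a different pair of cases at each assessment, so its planned post-test to follow-up contrast and any growth slope can show a change in effect that comes from the cases

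*Protocol article*

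**What the plan says.** The protocol article, under Primary outcome measures, states that for actual knowledge "six cases have been developed" and that at T0, T1 and T2 "participants will be presented with two new cases". Each case carries two general yes/no questions and "eight questions with multiple choice answers of which one is correct", one for the content of each module. The item count is not fixed: "The number of questions the participant has to answer depends on the answers given on the general questions".

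The perceived-knowledge and self-confidence instruments are handled differently: "During the three assessments of the effectiveness study participants receive the same two questionnaires".

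The Statistical analysis plan section makes no exception for actual knowledge. It offers ANCOVA with the pre-test as covariate for group differences "from pre-test to post-test, from pre-test to follow-up, and from post-test to follow-up". As an alternative, "HLM may be used in which individual growth curves over time are integrated in the model".

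The Discussion acknowledges that "the questionnaires have not yet been validated and the current trial is the first to provide information on the usefulness of the questionnaires". It does not mention that the form of the actual-knowledge test changes between assessments.

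**The concern.** A comparison of the arms at one assessment needs only that both arms sit the same test. A comparison of the arm difference across two assessments needs more: a given gain in knowledge must be worth the same number of points on both tests. For actual knowledge the tests differ, share no case, and have no earlier data to show that they are parallel.

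The score is bounded above, and guessing puts a floor under it. On an easy pair many controls are already near the top, so the same true gain yields fewer extra correct answers. On a poorly discriminating pair the gain is diluted. If the T2 pair is easier or less discriminating than the T1 pair, a stable effect looks like decay; if the order is reversed, it looks like growth. Actual knowledge is the only primary outcome that is not a self-rating, so a statement about whether its effect lasts would carry weight with readers.

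**Working it through.** **1. The forms do not overlap.** 2 cases × 3 assessments = 6, which is every case developed. No case links two occasions. Each pair has at most 2 × (2 + 8) = 20 questions, 16 of them multiple choice.

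**2. The plan's own figure.** With d = 0.45, two-sided α = 0.05 and power 0.80, n per arm = 2(1.96 + 0.84)²/0.45² ≈ 77.5, rounded up to 78 (156 in total). The article gives 77 per arm (154), where power is 0.797. The figure reproduces and is not in dispute. It supplies the effect and arm size used below.

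**3. When the form change cancels.** Write the expected score at time t as f_t(θ), where θ is true knowledge. The arm difference is f_t(θ + δ) − f_t(θ).
- If f_2 = f_1 + constant (a purely additive shift), the constant drops out and the T1-to-T2 change in the arm difference is unaffected.
- If δ = 0 at both times, the arm difference is zero on any pair.
- If δ ≠ 0 and f_2 has a different slope from f_1 over the relevant range, the arm difference changes although δ does not.

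**4. Illustration.** None of these item parameters is in the article: 16 multiple-choice items; P(correct) = 0.25 + 0.75/(1 + exp(−1.7a(θ − b))); θ with SD 1; true effect 0.45 SD at both T1 and T2. The reference pair has a = 1, b = 0.

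| Pair | Control mean of 16 | Arm difference, items | Standardised |
|---|---|---|---|
| Reference | 9.99 | 1.50 | 0.40 |
| 0.5 SD easier | 11.65 | 1.32 | 0.38 |
| 1 SD easier | 13.11 | 1.03 | 0.36 |
| 2 SD easier | 15.01 | 0.44 | 0.29 |

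The apparent loss on a pair 1 SD easier is (1.50 − 1.03)/1.50 ≈ 31% in raw items, but (0.40 − 0.36)/0.40 = 10% in standardised units.

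**5. Effect on the planned test.** The post-test to follow-up analysis is read here as T2 − T1 regressed on arm and T0 score, with 77 per arm and a within-person correlation of 0.8 in knowledge (assumed). There is no true change in effect in any row. Where a range is shown, it spans two separate simulations with the same constant effect.

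| T1 and T2 pairs | Mean false change, items | Trials declaring a change |
|---|---|---|
| Equal | 0.0 | 4.6% |
| T2 0.5 SD easier | – | about 7% |
| T2 1 SD easier | −0.47 | 12–16% |
| T2 much less discriminating (a = 0.4) | −0.65 | 18–25% |
| T1 1.5 SD easier | +0.78 | 36% |
| T2 2 SD easier | −1.05 | 54–60% |

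The mean changes agree with step 4: 1.03 − 1.50 = −0.47 and 0.44 − 1.50 = −1.06.

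**The case against.** - **The main trial question is not touched.** The aims concern whether the trained group improves more than the waitlist group. No hypothesis is stated about decay or growth between T1 and T2. A reader might infer that the actual-knowledge outcome as a whole is invalid or that its arm comparison is biased. The documents do not support that: the T0-adjusted comparisons at T1 and at T2 are protected by randomisation, and both are already planned. With no true effect at either time, the pairs create no false arm difference. This stands, and it limits the point to the time profile of the effect.
- **The cases share a template.** Each has the same layout and one question per module, which makes extreme differences between pairs less likely, and new cases limit recall of earlier answers. This stands as a reason to give the 2 SD rows little weight. It does not establish equal difficulty or discrimination.
- **The absence of equating is inferred.** A condensed article may omit rotation, equating or a scoring rule kept in the full protocol. This stands, and the recommendation is conditional on it. For the same reason, nothing shows that the pairs actually differ; a reader should not take that as established.
- **HLM is only permitted, and no slope is named as the target.** It would be too strong to say that every slope is uninterpretable, since an additive shift cancels in the group-by-time term. Within-arm slopes, however, absorb any form shift, and between-arm slopes absorb the non-additive part.
- **The raw-score distortion overstates the matter.** In standardised units it is much smaller. This stands. The test in the plan, though, is naturally run on scores, where the rejection rates above apply.

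**Conclusion.** The point holds in a limited form. As the article describes it, actual knowledge is not on one metric across assessments, yet the plan applies to it a post-test to follow-up group contrast and, optionally, growth curves. If training has a true effect, those analyses can report decay or growth that belongs to the cases.

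The size cannot be derived from the documents. With the assumed item model, a modest mismatch (0.5 SD) is nearly harmless at about 7% against a nominal 5%. A 1 SD mismatch gives 12–16%, a much less discriminating pair 18–25%, and an extreme 2 SD mismatch 54–60%. The standardised effect falls from about 0.40 to 0.29–0.37. All of this rests on the assumed guessing rate, item count, item parameters and within-person correlation, and on the pairs being neither rotated nor equated. The other two primary outcomes are unaffected. This is a cheap improvement, not a flaw in the main comparison.

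**What to change.** For actual knowledge only, state that inference rests on the arm differences at T1 and at T2, by ANCOVA with T0 as covariate or by HLM with time as a categorical factor. State also that no inferential claim will be made about T1-to-T2 change or a linear growth slope, unless the full protocol already rotates or equates the case pairs; if it does, the article should say so. The cost is wording, and one contrast on this outcome becomes descriptive. The analyses of perceived knowledge and self-confidence need no change on this account.

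Optionally, the three pairs could be rotated at random over T0, T1 and T2 for participants still to be enrolled, since data collection is online and recruitment was continuing. A main effect for pair alone corrects only mean difficulty. Ceiling and discrimination differences need pair-by-arm terms as well, or scores standardised within pair. Rotation would not repair the data of participants already assessed in a fixed order.

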### Secondary outcome measures

The secondary outcome is the satisfaction of the gatekeepers regarding the design of the e-learning modules. During the second assessment, participants from the experimental group are asked to complete a short evaluation questionnaire. In this questionnaire, characteristics of the e-learning modules are evaluated using 34 questions on expectations (2 items), relevance (2 items), design (5 items), interaction (2 items), cases and quizzes (11 items), overall satisfaction (6 items), website (5 items), and final commentary (1 item).

The questions are answered using the following format: a four-point Likert scale (17 items), multiple choice (3 items), rating (2 items), yes/no (4 items), and multiple responses (1 item). Seven of the questions are optional open questions which give the participant the opportunity to elaborate on their previous answers. Based on the answers the e-learning modules will be adjusted for implementation.

In addition, an attempt is made to improve the skills of the gatekeepers by providing them with frameworks, tips, and information in the e-learning modules. Due to privacy issues it is not possible to measure changes in this particular area as monitoring each gatekeeper, including an overview of false and correct referrals, would be required. However, participants from the experimental group are asked to rate several general statements on a four-point Likert scale as part of the evaluation questionnaire. One of these statements concerns the perceived gain in skills (‘By following the e-learning modules I have gained more skills in interaction with suicidal adolescents’). By asking the participants to rate this particular statement an overall indication of the impact of the e-learning modules on the skills of the participants can be obtained.

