## Abstract

**Background:**

Providing e-learning modules can be an effective strategy for enhancing gatekeepers’ knowledge, self-confidence and skills in adolescent suicide prevention. The aim of this study was to test the effectiveness of an online training program called *Mental Health Online* which consists of eight short e-learning modules, each capturing an important aspect of the process of recognition, guidance and referral of suicidal adolescents (12–20 years). The primary outcomes of this study are participant’s ratings on perceived knowledge, perceived self-confidence, and actual knowledge regarding adolescent suicidality.

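### The evaluation statement on skills gained, rated once by the experimental arm alone, can describe perceived benefit but cannot indicate the modules' impact on skills

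*Protocol article*

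**What the plan says.** All of this is in the protocol article, mainly in Secondary outcome measures.

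- **Purpose.** The modules try to improve skills as well as knowledge. The article concedes that change in skills cannot be observed directly: "Due to privacy issues it is not possible to measure changes in this particular area as monitoring each gatekeeper" would be needed, including a record of correct and false referrals.
- **Substitute.** In place of observation, "participants from the experimental group are asked to rate several general statements on a four-point Likert scale as part of the evaluation questionnaire". Then: "One of these statements concerns the perceived gain in skills". The statement reads "By following the e-learning modules I have gained more skills in interaction with suicidal adolescents".
- **Timing and arm.** "During the second assessment, participants from the experimental group are asked to complete a short evaluation questionnaire". The abstract also places the evaluation at post-test in the experimental group. A parenthesis under Assessments could be read as putting it in every assessment, but the other two places settle the timing.
- **Analysis.** The Statistical analysis plan section limits evaluation data to descriptive statistics in the experimental arm.
- **Inference drawn.** From this rating, "an overall indication of the impact of the e-learning modules on the skills of the participants can be obtained".

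Separately, Primary outcome measures describes a 16-item self-confidence questionnaire whose items are said to cover the skills and attitudes taught in the modules. The same form is given at T0, T1 and T2, and Study design has both arms complete it.

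**The concern.** Impact is a causal word. To indicate impact, a measure needs something to compare with: the same person's earlier value or, better in a randomised trial, the other arm. This item has neither. Its wording also states the cause (following the modules) and the direction (more skills), so the response scale records how far a respondent accepts a claim of benefit. Satisfaction, expectation, readiness to agree, ordinary work experience and a true module effect could all produce the same answer, and the data offer no way to separate them.

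Exposure adds to the difficulty. Under Interventions, participants choose which modules to follow, and Assessments anticipates that some modules will not be followed in the 14-day access window. The statement is addressed to the experimental group as a whole, so some may rate a gain from modules they hardly used.

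The privacy reason explains why referrals are not monitored. It does not explain why self-rated skill must be uncontrolled, since the trial already collects self-ratings from both arms.

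At stake is the report: a percentage agreeing could be presented as evidence of impact on skills and gain authority from the randomised design, although randomisation contributed nothing to it.

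**Working it through.** **1. The plan's own figure.** Sample size gives d = 0.45, two-sided alpha 0.05, power 0.80 and 77 per arm (154 in total).

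- n per arm = 2 × (1.960 + 0.842)² / 0.45² = 2 × 7.85 / 0.2025 ≈ 77.5, which rounds up to 78 (156 in total).
- Power at 77 per arm: 0.45 / √(2/77) = 0.45 / 0.161 = 2.79; 2.79 − 1.96 = 0.83; Φ(0.83) ≈ 0.797.

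The stated 154 reproduces within rounding. It was not set for the skills statement, and the point here does not depend on it.

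**2. What each source of information on skills can yield.**

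| | Evaluation statement | Self-confidence questionnaire |
|---|---|---|
| Items | 1 | 16, on skills and attitudes |
| Wording | gain attributed to the modules | statements of own ability |
| Arms | experimental only | both |
| Times | T1 | T0, T1, T2 |
| Change from baseline | no | yes |
| Randomised contrast | no | yes |
| Planned analysis | descriptive | between-arm; ANCOVA with pre-test as covariate, or HLM |

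**3. What the evaluation statement gives numerically.** With 77 respondents and agreement dichotomised, the 95% half-width is 1.96 × √(p(1 − p)/77). The values of p are assumptions:

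- p = 0.5: 0.112
- p = 0.7: 0.102
- p = 0.9: 0.067

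So agreement in one arm is known to within about 7 to 11 percentage points. More respondents would narrow the interval but would not turn it into an effect.

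**4. What a rating asked in both arms gives.** With 77 per arm and complete data, the standard error of a standardised mean difference is √(2/77) = 0.161. The 95% half-width is 1.96 × 0.161 = 0.316 SD before baseline adjustment, and adjustment would narrow it to the extent that baseline predicts outcome. Power for d = 0.45 is about 0.80. With assumed dropout of 10%, 20% or 30%, it is about 0.75, 0.70 or 0.65.

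These figures apply to any roughly continuous self-rated score collected in both arms. They show that a usable randomised comparison is within reach at the planned size.

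**The case against.** The strongest reply is that the article is candid and claims little. It says skill change cannot be measured, speaks of a perceived gain and an overall indication, and confines the data to description. Aims and hypotheses names only knowledge and self-confidence, the three primary outcomes do not include skills, and the secondary outcome is satisfaction with the modules' design. The stated use of the evaluation answers is to adjust the modules for implementation. No test or conclusion on effectiveness rests on the item. The abstract's mention of "knowledge, self-confidence and skills in adolescent suicide prevention" is a general remark about e-learning, not this trial's aim.

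Most of that stands, and it limits the seriousness of the point. It does not rescue the inference, because even a rough indication of impact needs a comparison and the sentence still uses the causal word.

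Some stronger readings are tempting but not supported:

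- *A reader might infer that this is the trial's only skill-related measure, so that no between-arm contrast on skills can be estimated.* The self-confidence questionnaire contradicts this. The absence of a contrast applies only to the evaluation statement.
- *A reader might infer that a formal skills outcome has been left uncontrolled.* Skills is not listed as an outcome.
- *A reader might infer that agreement with the statement is known to reflect mere acquiescence.* The article has no data on that. What can be said is that the design cannot tell the explanations apart.

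**Conclusion.** The point holds for one inference only. The evaluation statement can be reported as the share of the experimental arm that felt they benefited; it cannot indicate the modules' impact on skills. This follows from the arm, timing, wording and analysis that the article itself fixes, so no fuller analysis plan could recover a change or a contrast from this item.

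The reach is modest: the primary outcomes, their analysis and the sample size are untouched. It still deserves correction because it governs what the trial may say about skills and costs almost nothing to put right. The precision figures assume 77 per arm; those for a two-arm rating also assume complete data except where dropout is stated. The agreement and dropout rates are assumptions, not figures from the article.

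**What to change.** 1. Describe the statement as a perceived-benefit or satisfaction item and delete the claim that it indicates impact on skills. This is a wording change with no cost.
2. Base any statement about skills on the between-arm, baseline-adjusted comparison of the skill-related items in the existing self-confidence questionnaire, and label it as self-rated. No new data are needed. Name those items before outcome data are compared by arm, since the questionnaire mixes skills with attitudes, and present the result as supportive, since the full questionnaire is already a primary outcome. The Discussion's caveat that the questionnaires are not yet validated applies here too.
3. Optionally, add one neutrally worded self-rated skills item for both arms at the remaining assessments. The cost is one more online question. It would still be self-rated, and because recruitment began in September 2012, participants already past baseline would lack a T0 value. Given step 2, this is a refinement and not a necessity.
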